### Non-participants

Midwives are asked to fill in anonymous reply coupons for every woman who is not interested to participate in the study; including weeks of pregnancy, body weight and the reason for not participating. Women who decide not to participate after reading the information brochure at home, are asked to return a similar coupon. Characteristics of this group of non-participating women will be compared to those of women who do participate in the study.

### Randomisation

A computerized random number generator draws up an allocation schedule prestratified for midwifery practice; within practices respondents are allocated to the intervention group or to the control group at random. During the first telephone call with the research assistants – 2 weeks after the first appointment with the midwife; at 10–14 weeks of pregnancy – participants are informed about which group they are assigned to.

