### Selection of participants

Subjects participating in the study are recruited by participating midwives. During the intake, midwives invite women who are expecting their first child to participate. They introduce the study to the new client and give the women who are interested a brochure about the trial, to be read at home. After having received consent to do so, midwives write the name, telephone number, body weight, and expected date of delivery of interested women on a reply coupon, and send this coupon to the research team. Subsequently, a research assistant calls interested women within two weeks after the introduction to the study by her midwife. During this conversation the aim and implications of the study are explained again and the eligibility criteria are checked. Women are eligible for participation when they are:

1) expecting their first child;

2) able to read, write and speak Dutch;

3) within their first 14 weeks of pregnancy.

When a woman meets these inclusion criteria and wishes to join the study, she is included. After inclusion, an appointment is made for the baseline measurement at the midwifery practice. Informed consent forms will be obtained from each participant.

This study focuses on women who are expecting their first child, and who will deliver their first child during the term of the study. By excluding pregnant women who already have children, the study population is expected to be more homogeneous. Mothers that are expecting their second or third child, have already experienced at least one pregnancy and the weight change related to that pregnancy. Based on the experiences in their previous pregnancy, these women already have specific expectations and attitudes concerning weight changes and lifestyle during pregnancy. Besides, the daily situation of women with children is different. Because of the transition from a household of adults to a family life, their lifestyle has already been changed. So, focusing on women without children limits disturbing effects of parity on outcome measures.

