### Content of the counselling sessions

Each counselling session is structured in a uniform way (see Table 1). During the first visit the counsellor talks about weight gain during pregnancy and the distribution of this 'extra' weight among different tissues. After this, the IOM guidelines are introduced and the dependence of healthy weight gain during pregnancy on pre-pregnancy body mass index is discussed. Weight and height is assessed and pre-pregnancy BMI is calculated, after asking for pre-pregnancy weight, in order to categorize women in pre-pregnancy BMI-groups: underweight, normal weight, overweight or obese.

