### Measurements

Participants in both the intervention and control group are invited for six measurement appointments in the period during and after pregnancy. The baseline measurement is at 15 weeks of pregnancy. Data are collected at: 15, 25, and 35 weeks of pregnancy and at 8, 26, and 52 weeks after delivery. At these occasions the research assistants perform anthropometrical measurements in all midwifery practices and register the primary outcome measures. Blood samples are collected in five of the eight participating practices by trained assistants; in the other three practices the assistants are not schooled for intravenous punctures and consequently no blood samples can be collected. Each assistant is permanently linked to one or more practices, so that participants are measured by the same person at each occasion. All participants receive questionnaires by ordinary mail one week before each measurement appointment. They are asked to complete the questionnaires and hand these in when they visit the research assistant for a measurement appointment. The assistant personally checks the questionnaires for missing data. The following measures are assessed:

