### Primary outcome measures

#### Body weight and BMI

Body height is measured on bare feet by means of a wall-mounted height scale (SECA 206), with an accuracy of 0.1 cm. Calibrated electronic scales (SECA 888) are used to determine body weight of the participants in underwear and pants, with an accuracy of 0.1 kg. Both weight and height is measured twice, and the mean value of the two measurements is computed and used to calculate individual body mass index (BMI, kg/m^2^) at 26 and 52 weeks after pregnancy. Pre-pregnancy BMI is based on self reported pre-pregnancy weight.

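### Women learn their group at 10–14 weeks, before the 15-week baseline, so baseline self-reports, and possibly the reported pre-pregnancy weight, come from women who know their arm

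*Protocol article*

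**What the plan says.** All references are to the Methods of the protocol article.

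- **Selection of participants.** A research assistant telephones interested women: "During this conversation the aim and implications of the study are explained again and the eligibility criteria are checked". Then: "After inclusion, an appointment is made for the baseline measurement at the midwifery practice". Before this call, the midwife has already written the woman's body weight on a reply coupon.
- **Randomisation.** The first call, at 10–14 weeks, is also where allocation is disclosed: "participants are informed about which group they are assigned to".
- **Measurements.** "The baseline measurement is at 15 weeks of pregnancy", and "All participants receive questionnaires by ordinary mail one week before each measurement appointment".
- **Intervention.** The first counselling session is at 18 weeks, and the brochure follows that session.
- **Body weight and BMI.** "Pre-pregnancy BMI is based on self reported pre-pregnancy weight". No time of collection is given.
- **Content of the counselling sessions.** In the first session, after the IOM guidelines have been introduced: "Weight and height is assessed and pre-pregnancy BMI is calculated, after asking for pre-pregnancy weight". The result places the woman in a BMI group, which decides her weight gain chart.
- **Statistical analyses.** The five domains include total gain, the percentage above the IOM guideline, retention at six months and one year, physical activity, and behavioural determinants. No reference weight is named for gain or retention.

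**The concern.** A baseline is useful because allocation cannot have touched it. Here the women cannot be blinded, have had the aim of the study explained to them, and know their group before they complete the first questionnaire. Answers on activity (SQUASH), eating, attitude, self-efficacy and stage of change may differ between arms for that reason alone. If such values are later used as starting points or covariates, part of what is adjusted for could be a consequence of allocation.

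Pre-pregnancy weight raises the same question. It fixes the BMI group and hence the IOM limits, so a report that depends on arm can change who counts as exceeding them. If gain and retention are measured from it, the difference in reporting enters those outcomes directly.

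Finally, a woman disappointed by her group can leave before any baseline visit has taken place.

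**Working it through.** **1. Order of events, from the stated times**

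| Week of pregnancy | Event | Arm known to the woman? |
|---|---|---|
| 9–12 | Midwife's intake; coupon with body weight | No |
| 10–14 | First research call: eligibility checked, group disclosed | From here on, yes |
| about 14 (15 − 1) | Baseline questionnaires mailed | Yes |
| 15 | Baseline visit | Yes |
| 18 | First counselling session (intervention arm only); pre-pregnancy weight asked | Yes |

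The gap from disclosure to the baseline visit is 15 − 14 = 1 week to 15 − 10 = 5 weeks. The gap from the baseline visit to the first session is 18 − 15 = 3 weeks. The coupon weight is the only value with a stated collection point before disclosure.

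**2. Which outcomes are exposed**

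- *Exposed through reporting:* SQUASH, eating and determinant questionnaires at baseline; IOM exceedance, through the BMI group; total gain and retention, if they are measured from reported pre-pregnancy weight.
- *Exposed only through changed behaviour over 1–5 weeks or selective withdrawal:* weight and skinfolds at 15 weeks, which the Blinding section assigns to examiners unaware of allocation, and accelerometry.
- *Not directly exposed:* BMI at six months postpartum, computed from duplicate measured weight and height.

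**3. The plan's own figure**

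The sample size is set for a BMI difference of 0.8 kg/m² at six months, SD 2.0, two-sided 5%, power 0.80. The usual formula gives 2 × (1.960 + 0.842)² × 2.0² / 0.8² = 98.1, so 99 per group against 110 stated. The stated number is on the safe side (power about 0.84 at 110 per group). The dropout step reproduces: 220 / (1 − 0.20) = 275. None of this bears on the point, except to show that the powered comparison is of a measured postpartum value with no reference weight.

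**4. Illustration for outcomes that subtract pre-pregnancy weight**

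Assumptions not in the article: height 1.70 m (1.70² = 2.89 m²) and a between-arm shift in mean reported pre-pregnancy weight of 0 to 1.0 kg. Shift in BMI units = kg / 2.89.

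| Assumed shift (kg) | Shift (kg/m²) |
|---|---|
| 0 | 0 |
| 0.25 | 0.09 |
| 0.5 | 0.17 |
| 1.0 | 0.35 |

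Suppose also that the SD of 2.0 applied to such a change outcome, which the article does not say. With 110 per group the standard error is 2.0 × √(2/110) = 0.27. With no true effect, the two-sided 5% error would become about 6.2%, 9.8% and 25% for the three non-zero rows.

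**The case against.** The strongest reply is that the trial's main comparison is untouched, and that stands. A reader might set a 1.0 kg shift against the 0.8 kg/m² target (0.35 / 0.8 = 43%) and conclude that nearly half the detectable effect could be an artefact. The article does not support this: the target concerns measured BMI at six months postpartum, to which reported pre-pregnancy weight contributes nothing. The size of any shift is also an assumption. Nothing in the article shows that hearing one's group, before any counselling, changes the weight a woman reports.

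Four other inferences also go too far:

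- *That the counsellor's value is the outcome reference.* Its stated purpose is to choose a chart. Controls have no counselling session, so a value for both arms needs a common source. The full protocol may name that source and its timing.
- *That pre-pregnancy weight is tied to no visit at all.* One contact is named, in the intervention arm.
- *That early behaviour change is subtracted from the effect.* The Statistical analyses section names neither change from 15 weeks nor adjustment for baseline.
- *That women who leave after disclosure have no earlier data.* Their coupon weight exists. That such withdrawals differ by arm is a possibility, not a finding.

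What the reply does not remove is the order itself. Disclosure before baseline is fixed in the text, not left out by condensation. Blinded examiners protect measured values, not self-report, and two of the five analysis domains (activity and behavioural determinants) rely wholly or mainly on questionnaires.

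**Conclusion.** The point holds in limited form. Baseline self-reports are given after women know their arm, withdrawal can occur between disclosure and the baseline visit, and self-reported pre-pregnancy weight is not placed before disclosure. At risk are activity, behavioural determinants, IOM exceedance, and gain or retention if these are referenced to pre-pregnancy weight. The powered BMI comparison is not directly biased.

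The size cannot be derived from the article. The 0.09–0.35 kg/m² rests on the assumed height and on an assumed shift of 0.25–1.0 kg; the true shift may be zero. The order of events is certain and its effect is not, so this is a moderate weakness that is cheap to remove, not one that invalidates the design.

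**What to change.** **Women not yet informed.** Release allocation only after the 15-week visit and its questionnaires are complete. Ask every woman her pre-pregnancy weight in the existing eligibility call, before allocation is released, and use only that value for IOM classification, gain and retention. The counsellor's answer should serve the chart alone.

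**Women already informed.** Use the coupon weight as a pre-disclosure covariate or as the reference in a sensitivity analysis, bearing in mind that it is an early-pregnancy weight recorded at intake and not a pre-pregnancy weight. Report withdrawals by arm between disclosure and 15 weeks. The coupon does not help the questionnaires, so their baseline values should be described as collected after disclosure.

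**Cost.** One extra question in a call that is already made, notification 1–5 weeks later, and about three weeks instead of four to eight (18 − 14 to 18 − 10) in which to book the first session.

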### Blinding

All anthropometric outcome measures are assessed by independent examiners unaware of group allocation. Participants cannot be blinded for the intervention, but are asked not to reveal information about their treatment to the examiners. The key of coding concerning group assignment is only known by the programmer of the database that is used during the study.

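### The staff role that tells women their allocation also measures the primary outcomes, so the statement that examiners are unaware of allocation is not supported as written

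*Protocol article*

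**What the plan says.** Four sections of the protocol article bear on this point.

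- **Selection of participants:** the first contact after the midwife's introduction is by telephone. "Subsequently, a research assistant calls interested women within two weeks after the introduction to the study by her midwife". The study is explained again and eligibility is checked in that conversation.
- **Randomisation:** the allocation is given in the same contact. "During the first telephone call with the research assistants", placed at 10–14 weeks of pregnancy, "participants are informed about which group they are assigned to".
- **Measurements:** "At these occasions the research assistants perform anthropometrical measurements in all midwifery practices and register the primary outcome measures". In addition, "Each assistant is permanently linked to one or more practices, so that participants are measured by the same person at each occasion".
- **Blinding:** "All anthropometric outcome measures are assessed by independent examiners unaware of group allocation". It adds that "The key of coding concerning group assignment is only known by the programmer of the database that is used during the study", and that "Participants cannot be blinded for the intervention, but are asked not to reveal information about their treatment to the examiners".

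**The concern.** One job title, research assistant, appears at both ends of the chain: in the call where the group is disclosed and at the visits where the primary outcomes are recorded. Whoever tells a woman her group knows it. If that person later measures her, the examiner is not unaware of allocation for that woman, and the fixed pairing of measurer and participant would carry this through the whole follow-up.

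Participants cannot be blinded here, so assessor blinding is the main protection the protocol offers against biased measurement. The one safeguard described for the visits is the request that women keep their treatment to themselves. That does not help if the assistant was the source of the information. If the separation is absent in practice, a report of blinded outcome assessment would be wrong, and a skinfold difference between groups could partly reflect what the observer expected.

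**Working it through.** No arithmetic applies, so the check sets the statements side by side.

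**Step 1: who takes part in the disclosure.** Selection of participants gives the call to a research assistant. Randomisation places the disclosure in the first call with the research assistants. The verb is passive, but no other staff member is named in that call. The natural reading is that the assistant states the group.

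**Step 2: who measures.** Measurements names the research assistants, in all practices, each tied to one or more practices, with one person measuring a given woman throughout. Counsellors, midwives and the database programmer are named as distinct roles elsewhere. Calling assistants and measuring assistants are not.

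**Step 3: test the Blinding section under each reading.**

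| Reading | Examiners unaware of allocation? | Key known only to the programmer? |
|---|---|---|
| The same assistant calls and measures a woman | False for that woman | Not literally true |
| Different assistants call and measure | Can be true, but needs a rule the text does not state | Not literally true |

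The last column fails under both readings because individual allocations must reach whoever informs the women, and counsellors must know whom to see. If the key means only the master list, the sentence can stand, but it then says nothing about who holds individual allocations.

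**Step 4: timing.** Disclosure falls at 10–14 weeks and the baseline measurement at 15 weeks. All six measurement occasions, baseline included, therefore come after any unblinding in the call.

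**Step 5: which outcomes are exposed.** The primary outcomes are body weight, BMI and skinfold thickness.

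- Weight is read from calibrated electronic scales to 0.1 kg and height from a wall-mounted scale to 0.1 cm. Each is taken twice and averaged, and BMI follows from them. There is little room for an observer's expectation.
- Skinfolds are read by calliper at four sites. Each site is read twice, with a third reading if the first two differ by more than 1.0 mm. The trigger is a numeric rule, but it acts on the observer's own readings, and placing and reading the calliper depend on the observer.

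**Step 6: size.** The document gives no between-observer variation and no figure for how many women would be measured by the assistant who called them. The size of any bias cannot be calculated.

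**The case against.** The strongest reply is that a shared title is not a shared person. The permanent link concerns measurement only, and no sentence says that the caller of a given woman is also her measurer. The Blinding section calls the examiners independent and unaware. If the assistants divided the two tasks, the statements about calling, measuring and examiner blinding could all be true. A journal article also leaves staffing details to the full protocol.

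The part about individuals stands: the text does not prove that any one assistant does both tasks for the same woman. The rest does not remove the problem. The article does more than omit a detail: it assigns both tasks to one named role and then asserts a blinding that this assignment does not support.

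Three stronger readings are tempting and are not supported.

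- **Blinding is broken for all 275 planned women at every visit.** This needs every caller to be the measurer of every woman she called, which the document does not say.
- **Allocation concealment is broken because eligibility and disclosure share one call.** No passage says the assistant sees the assignment before eligibility is settled. Release after inclusion, within the same call, fits the text.
- **No primary result could be told apart from observer effect.** This is too broad. Weight and BMI come from calibrated instruments, the sample size rests on BMI, and skinfolds are not named among the five domains under Statistical analyses.

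**Conclusion.** The concern holds as a conflict between stated passages. As written, the Randomisation and Measurements sections do not support the Blinding section's claim of unaware examiners, and the claim about the key cannot be literally complete. This conclusion assumes that research assistants means the same staff group wherever the article uses it, and that the person speaking to the woman in the call is the one who tells her the group.

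How many women are affected is unknown: it runs from none, if calling and measuring were kept apart, to all, if they were not. The consequence is a risk of observer bias, concentrated in skinfold thickness, with no derivable size. It gives no ground for saying that the weight or BMI comparison is invalid.

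**What to change.** **Main change.** Release each allocation only after inclusion is confirmed. Have it disclosed by someone who measures no outcomes: by letter, or by the counsellor. Give measuring assistants appointment lists that do not show the arm. Reword the sentence on the key to say who holds the master list and who receives individual allocations.

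**Minimum change.** If assistants go on disclosing allocation, state that an assistant never measures a woman whose allocation she disclosed.

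**Women already informed by their measuring assistant.** Keep the same measurer. Changing her would break the protocol's own rule of one measurer per woman and add between-observer variation to the skinfolds. Record for each woman whether her measurer knew the allocation, and report a sensitivity analysis of skinfold thickness, for example the group effect with and without these women. If nearly all women turn out to be in this position, that analysis cannot help. The report should then say that skinfold assessment was not blinded.

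**Cost.** One call or letter is reassigned to existing staff, and no extra assessor is needed. Using the counsellor brings the person who delivers the intervention into brief contact with control women; a letter avoids this.

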### Intervention

The New life(style) intervention program consists of 5 individual counselling modules together with a general information brochure. In the modules the counsellors discuss with the women allocated to the intervention group, how to control their weight during and after pregnancy, and how to maintain or optimize a healthy lifestyle in a period of drastic physical and mental changes. Women go through these counselling sessions in 30 weeks; they have appointments with their counsellor at 18, 22, 30 and 36 weeks of pregnancy and at 8 weeks postpartum. The counsellors, in charge of these counselling sessions, are members of the research team (see Counsellors). They are permanently linked to a specific midwifery practice. In this way, all women in the intervention group are assigned to a personal counsellor, facilitating the contact between participant and counsellor. Each counselling session takes 15 minutes, but the first session takes approximately half an hour, to explain the aim of the study and the intervention. The content of the first module is generalised and summarised in an information brochure, which the participants receive after the first counselling session of the intervention program.

